#### **9.3.1.1. Effects on Hepatic, Renal, and Hematologic Function**

If the results of any blood test demonstrate a rise to 2.5 times the upper limit of normal in AST, ALT, or bilirubin, these laboratory results will be documented as an AE. An additional blood sample will be drawn from the subject, and the tests will be repeated. The samples will also be tested serologically for HBsAg, and HCV, and HIV will be tested by NAT within a 1-week period.

#### **9.3.2. Direct Coombs' Test**

If any Direct Coombs' Test is positive, the central laboratory must notify the site investigator and the CRO of the results of all the above tests within 2 business days.

#### **9.4. Viral Transmission**

If any of the tests for HBV, HCV, HIV, or Parvovirus B19 suggest a change in viral status of the subject, the tests will be repeated by the central laboratory as soon as possible. If a change in viral status is confirmed by a second independent test, the reserve sample taken before the first infusion of GAMMAPLEX will be re-tested in the same laboratory. The central laboratory will inform the sponsor and the CRO within 12 hours of the change in viral status.

#### **9.5. Physical Examination**

Physical examination will be performed by personnel qualified to perform such procedures in the state in which the study site is located. Elements of the exam are as follows:

- General appearance
- Head, eyes, ears, nose, throat
- Chest
- Cardiovascular
- Respiratory
- Abdomen
- Musculoskeletal
- Genitourinary
- Skin
- Assessment of bleeding/hemorrhage (see Appendix 1)
- Other

Any clinically significant change from baseline in any system will be recorded as an AE.

## 10. STATISTICAL METHODS

### 10.1. Sample Size

The calculation of sample size was based on the primary efficacy variable, i.e., the percent of subjects attaining a platelet count of  $\geq 50 \times 10^9/L$  by Day 9 on the first course of GAMMAPLEX. A minimum of 31 evaluable subjects will be enrolled in the study. However, when 27 evaluable subjects have completed Day 9, a partial analysis may be conducted, and the response rate ( $P_1$ ) calculated and compared with that of the historical control,  $P_0$  (lower bound of 95% confidence interval) is greater than 0.60, to determine the power achieved at this interim stage. The response rate estimated at this stage will be used to re-estimate the sample size necessary at the end of the study to achieve a power of 80% to detect the desired difference.

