| Number of subjects: A minimum of 31 evaluable subjects will be enrolled in the study. The final number will depend on the number estimated by the power calculation in the partial analysis to be performed when at least 27 evaluable subjects have completed Day 9.                                                                                                                                                                                                                                                                                                                                                                                                                                                                                                                                                                                                                                                                                                                                                                                                                                                                                                                                                                                                                                                                                                                                                                                                                                                                                                                                                                                                                                                                                                                                                       |                                                                                                                       |

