### **5.2. Overall Study Design**

This will be a multicenter, open-label study conducted at approximately 25 clinical sites in the U.S., India, and Argentina. A minimum of 31 evaluable subjects will be enrolled in the study.

The final number will depend on the number estimated by the power calculation in the partial analysis.

After screening and enrollment, subjects will initially receive infusions of GAMMAPLEX on Days 1 and 2 (first treatment course). Subjects will be assessed for safety and efficacy on Days 3, 5, 9, 14, 21, and 32; then they will then return for a final follow-up visit (End of Study), to include viral safety tests on Day 90.

If the platelet count is not maintained for the desired length of time after the first course of GAMMAPLEX, and at the discretion of the study investigator and subject/guardian, subjects may receive up to 2 additional courses of GAMMAPLEX within the 32 to 90 days after the first dose. Subjects who receive additional treatments will attend all safety and efficacy follow-up visits as scheduled for the first treatment course. In addition, they will be assessed for safety prior to each additional dose of GAMMAPLEX and 3 days after the end of each treatment course. All subjects will attend one End of Study visit, which will be 90 days, approximately 3 months, after the first infusion of the last course of GAMMAPLEX (see Section 5.3.1.6).

Efficacy data will be collected and analyzed for the first course of GAMMAPLEX only.

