### 10.3. Efficacy Analyses

#### 10.3.1. Analysis of the Primary Efficacy Variable

The primary efficacy data will be analyzed by using the ITT.

The percent of subjects attaining a platelet count of  $\geq 50 \times 10^9/L$  by Day 9 will be compared with the historical response rate of  $>60\%$ . A 1-sided 95% confidence interval will be constructed for the percent of subjects attaining a platelet count of  $\geq 50 \times 10^9/L$  by Day 9 for GAMMAPLEX. If the lower bound of this confidence interval is  $>0.60$ , GAMMAPLEX will be declared effective for the treatment of chronic ITP.

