### **10.5.2. Partial Analysis**

A partial analysis may be performed when at least 27 evaluable subjects have completed Day 9. The observed response rate will be estimated and compared with the historical control of  $>0.60$  to re-estimate the sample size.

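### The sample size re-estimation uses the response rate seen in about 27 subjects as its target, with no fixed alternative, no maximum and no rule at or below 0.60, so 80% power is not a property of the design

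*Protocol*

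**What the plan says.** Section 10.1 ties the sample size to the Day 9 platelet response. It sets a floor, also given in the synopsis ("A minimum of 31 evaluable subjects will be enrolled in the study"), and continues that "when 27 evaluable subjects have completed Day 9, a partial analysis may be conducted". The rate found there is to be "used to re-estimate the sample size necessary at the end of the study to achieve a power of 80% to detect the desired difference". The abbreviation list defines P1 as the response rate at the partial analysis, so P1 is an observed quantity and not a planning assumption. The reference value is 0.60.

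Section 10.5.2 repeats the rule ("The observed response rate will be estimated and compared with the historical control of" more than 0.60) and sets the trigger at 27 or more subjects. Section 5.2 says: "The final number will depend on the number estimated by the power calculation in the partial analysis". Both 10.1 and 10.5.2 make the partial analysis optional.

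Success is defined in section 10.3.1: "A 1-sided 95% confidence interval will be constructed for the percent of subjects attaining a platelet count of" at least 50 × 10⁹/L by Day 9, and the product is declared effective if the lower bound exceeds 0.60. The interval method is not named. No section gives a number for the desired difference, an assumed rate behind the 31, a maximum sample size, or an action if the observed rate is 0.60 or lower.

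**The concern.** A power statement means something when the alternative is chosen beforehand. Here the alternative is an estimate from about 27 subjects, and the required sample size varies with the inverse square of its distance from 0.60. A change of one or two responders can move the target from tens to hundreds or more than a thousand. Below 0.60 the formula has no solution.

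Eighty percent is the only power figure in the protocol. If the rule does not hold it, the reader does not know what the trial can detect. Because the branch at or below 0.60 is unwritten, the decision would be made after the data are seen in an open-label study. The further step in 10.1 of working out the power reached so far from the same observed rate adds nothing beyond that rate.

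**Working it through.** **Inputs.** Reference rate 0.60 and target power 80% (10.1); one-sided 95% bound, taken as one-sided 5% (10.3.1); floor 31 and partial analysis at 27 (10.1). Assumption: exactly 27 subjects are used. With more, the cut-points shift.

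**The plan's own figure.** The 31 cannot be reproduced, because no assumed rate is given. Solving backwards with the formula below gives N = 33 at 0.80 and 30 at 0.81; an exact binomial calculation gives 30 to 33 at 0.82. So 31 is compatible with an unstated alternative of about 0.80 to 0.82.

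**Step 1: sample size by partial result.**

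N = [(1.645·√(0.60·0.40) + 0.842·√(p(1−p))) / (p − 0.60)]², with p = x/27.

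Example, x = 18: p = 0.6667. The numerator is 1.645·0.4899 + 0.842·0.4714 = 1.203. Dividing by 0.0667 gives 18.04, and squaring gives about 325.4, so N = 326.

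| Responders of 27 | Rate | N (normal) | N (exact range) |
|---|---|---|---|
| ≤16 | ≤0.593 | none exists | none exists |
| 17 | 0.630 | 1,674 | 1,671–1,736 |
| 18 | 0.667 | 326 | 325–347 |
| 19 | 0.704 | 132 | 135–149 |
| 20 | 0.741 | 70 | 71–77 |
| 21 | 0.778 | 43 | 45–51 |
| 22 | 0.815 | 28, so 31 | 30–33 |
| ≥23 | ≥0.852 | ≤20, so 31 | ≤24, so 31 |

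Going from 18 to 17 responders raises N by 1,674 − 326 = 1,348.

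**Step 2: how often the difficult cases arise (binomial, n = 27).**

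| True rate | 16 or fewer (no N) | 17 or 18 (N ≥ 326) |
|---|---|---|
| 0.70 | 16% | 27% |
| 0.80 | 1% | 6% |

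**Step 3: overall power of the rule.** For each x from 0 to 27, set N to the larger of 31 and the Step 1 value (31 if x ≤ 16). Take r as the smallest count with P(Bin(N, 0.60) ≥ r) < 0.05, and sum

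Power(p) = Σ P(Bin(27, p) = x) · P(x + Bin(N − 27, p) ≥ r).

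| True rate | Probability of success |
|---|---|
| 0.60 | 0.053 (type I error) |
| 0.65 | 41% |
| 0.70 | 70% |
| 0.75 | 88% |
| 0.80 | 96% |

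Stopping at 31 after 16/27 or fewer is the same as failing: at most 16 + 4 = 20 responders are possible, and 24 are needed with the exact bound. If such a trial instead ran on to a large cap of 350 to 1,700, type I error would rise to about 0.066–0.074.

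**Step 4: power of the floor, N = 31.**

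| Interval | Responders needed | Type I error | Power at 0.80 | at 0.82 | at 0.85 |
|---|---|---|---|---|---|
| Exact or Wilson | 24 | 0.033 | 73% | 82% | 92% |
| Wald | 23 | 0.074 | 85% | 91% | 97% |

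**The case against.** The strongest reply is that the extremes are rare where the trial was probably planned. If the true rate is 0.80, the no-solution case has 1% probability and N of 326 or more has 6%; the rule's power there is well above 80%. This stands, and it limits the size of the point. It does not remove it, because the protocol states no assumed rate and so cannot rely on 0.80.

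A second reply is that the SAP, which is not shown, may supply a cap or a fixed alternative. It may, but section 10.1 does not leave the matter open. It states a rule, and that rule plugs in the observed rate.

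Four stronger readings are tempting and are not supported:

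- A reader might infer that the trial would run to nearly 1,700 subjects automatically. Section 14.1 requires approvals for a change that increases the number treated, and section 14.2 lets the sponsor stop at any time. Neither is a statistical maximum, but both are brakes.
- A reader might infer that the final test is invalid. Under failure or stopping at 31 after 16/27 or fewer, type I error is about 0.053 with the exact bound. Larger inflation needs continuation to a large cap, which the protocol does not describe.
- A reader might say flatly that 31 subjects are underpowered at 0.80. That depends on the interval method, which section 10.3.1 does not name: 73% with exact or Wilson, 85% with Wald.
- A reader might infer that the sample size is undefined if the optional analysis is skipped. Section 5.2 is loosely worded, but 31 is the natural reading of 10.1.

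**Conclusion.** The point holds as a should-fix. The protocol sizes the trial on a rate estimated from about 27 subjects, with no fixed alternative, no maximum and no rule at or below 0.60. The 80% is therefore a nominal input to a formula, not the power of the procedure. That power runs from about 41% at a true 0.65 to about 96% at 0.80. The shortfall lies at the lower true rates; it would be wrong to say that the rule falls below 80% everywhere, since it exceeds 80% at 0.75 and above.

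These figures assume exactly 27 subjects at the partial analysis, normal-approximation sizing, an uncapped N, an exact final bound on all subjects, and failure or N = 31 after 16/27 or fewer. Other choices move the figures. They do not supply the missing alternative, maximum or branch.

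**What to change.** In section 10.1, with matching text in the synopsis, 5.2 and 10.5.2:

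1. State 0.60 and a fixed alternative chosen in advance, and size the trial on them.
2. Replace the 80% claim by the power of the minimum of 31, with the interval method named, using the Step 4 figures. If Wald is chosen, disclose its type I error of 0.074.
3. If re-estimation is kept, state in advance a maximum chosen by the sponsor and the action at an observed rate of 0.60 or lower. Quote the enumerated power and type I error of the whole rule.
4. Say that the sample size stays at 31 if the partial analysis is not done.
5. Delete the step that works out the power reached at the partial analysis.

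The change is to wording only. Its cost is that the stated power looks less favourable at lower true rates, and a tight maximum gives up real power there. As an illustration only, since nothing in the protocol supports that number, a maximum of 60 with the exact bound gives 44–45% at 0.70, 75–76% at 0.75 and 94% at 0.80.

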### 10.2. Analysis Population

Any subject who started treatment with GAMMAPLEX and whose central laboratory results taken prior to infusion on Day 1 are within specified protocol parameters, will be included in the intent-to-treat (ITT) population for analysis of efficacy and safety. Any subject whose central laboratory results from Day 1 are outside of the required parameters, will be included in the safety analysis only.

Additionally, subjects aged 6 to 17 years (applicable only to subjects enrolled before implementation of Protocol Version 7) will be analyzed separately from the remaining samples for any differences in response to treatment. This subset will be analyzed in the same manner as the total sample.

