| Methodology: Efficacy: The primary efficacy variable will be analyzed using the intent-to-treat population (ITT). The percent of subjects attaining a platelet count of $\geq 50 \times 10^9/L$ by Day 9 will be compared with the historical response rate of >60%. A 1-sided 95% confidence interval will be constructed for the percent of subjects attaining a platelet count of $\geq 50 \times 10^9/L$ by Day 9 for GAMMAPLEX. If the lower bound of this confidence interval is >0.60, GAMMAPLEX will be considered effective for the treatment of chronic ITP. 
The secondary efficacy variables will be analyzed by: 1) using the method of Kaplan and Meier to produce plots of the distribution of the time for which the platelet counts remain <math>\geq 50 \times 10^9/L</math>; 2) a 95% confidence interval for the median time will be constructed.
 
Bleeding/hemorrhage events will also be summarized by number and percent (Appendix 1).
 
Safety: The proportion of infusions where an AE occurs during an infusion or within 72 hours after the end of the last infusion (Day 2) will be tabulated. A summary table, including number of subjects with AEs, SAEs, deaths, withdrawn due to AEs, and product-related AEs will be produced. The nature, severity and frequency of all AEs will be listed.
 
Summary tables for laboratory measures of hepatic, renal, and hematologic function will include the following: descriptive statistics (mean, standard deviation, median, maximum and minimum) for original values and change from baseline for all continuous variables; incidence (number and percent) of clinically significant, treatment-emergent abnormal values (TEAVs); shift tables will be used to show the incidence of new or worsening clinically
 |                                                                                                                       |

|                                                                                                                          |                                                                                                                       |
|--------------------------------------------------------------------------------------------------------------------------|-----------------------------------------------------------------------------------------------------------------------|

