## 6. STUDY POPULATION

### 6.1. Inclusion Criteria

1. Males and females aged between 18 and 70 years
2. Confirmed diagnosis of chronic ITP of at least 6 months duration.
3. Platelet count  $\leq 20 \times 10^9/L$  at enrollment (local laboratory).
4. Absence of other conditions that, in the opinion of the investigator, could cause thrombocytopenia.
5. If subjects are currently being treated with corticosteroids the treatment regimen/dose must have been stable (for a minimum of 2 weeks before Day 1). However, subjects must remain on a stable treatment regimen. If there is any intent to alter the corticosteroid treatment regimen (e.g., tapering of corticosteroids) before Day 10, subjects may not be included in the study. If possible, doses of corticosteroids or other immunosuppressant medications should remain constant until Day 32. The primary efficacy variable of the study is the platelet count at Day 9. Therefore, changing the subject's medication regimen should be avoided in order to reduce the variables that could have an effect on the platelet count.
6. If subjects are currently being treated with cyclophosphamide, azathioprine or attenuated androgens, the treatment regimen and dose must have been stable for a minimum of 2 months before Day 1. However, if there is any intent to alter the treatment regimen before Day 10, subjects may not be included in the study. If possible, doses of corticosteroids or other immunosuppressant medications should remain constant until Day 32. The primary efficacy variable of the study is the platelet count at Day 9. Therefore, changing the subject's medication regimen should be avoided in order to reduce the variables that could have an effect on the platelet count.
7. Splenectomized subjects and both Rh(D)+ and Rh(D)- subjects can be included.
8. The subject has signed an informed consent form (subjects must be at least 18 years old), and/or the subject's legal guardian has signed the informed consent form if indicated, not more than 6 months prior to Day 1 (see Section 11.3).
9. If a subject is a female of child-bearing potential, she must have a negative result on a urine-based HCG pregnancy test.
10. If a subject is a female who is or becomes sexually active, she must practice contraception by using a method of proven reliability for the duration of the study.

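### Section 10.2 wants to know whether children respond differently, but prescribes a one-group analysis against 0.60 that contains no comparison with the other subjects

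*Protocol*

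**What the plan says.** Section 10.2 of the protocol states the purpose of the subset analysis: subjects aged 6 to 17 years "will be analyzed separately from the remaining samples for any differences in response to treatment". It limits the group to those already in the study ("applicable only to subjects enrolled before implementation of Protocol Version 7"). It then gives the method: "This subset will be analyzed in the same manner as the total sample".

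For the primary variable, the method for the total sample is in section 10.3.1: "A 1-sided 95% confidence interval will be constructed for the percent of subjects attaining a platelet count of" at least 50 × 10⁹/L by Day 9. The decision rule attached to it reads, in the synopsis, "If the lower bound of this confidence interval is >0.60, GAMMAPLEX will be considered effective for the treatment of chronic ITP". For the secondary variables, section 10.3.2 gives Kaplan-Meier plots with an interval for the median, and descriptive bleeding summaries.

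Section 6.1 now admits only "Males and females aged between 18 and 70 years". Section 10.1 plans for at least 31 evaluable subjects, not split by age, and sets its 80% power target for the study as a whole.

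**The concern.** The aim and the method in section 10.2 belong to different questions. A search for differences in response asks how the children's rate compares with the rate in the other subjects. The prescribed primary analysis asks whether one group's rate lies above a fixed 0.60 and uses no data from the other group. The secondary analyses are also one-group summaries.

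This goes beyond a detail left to the SAP. The protocol does prescribe a method, and a SAP that follows it would inherit the mismatch. Taken literally, the method also carries the 0.60 rule into a subset for which it was not sized. A reader of the report could then see adults meeting the rule and children missing it, and take this as evidence about age when it may show only that there were few children.

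**Working it through.** **Aim against method.** None of the analyses that section 10.2 points to contrasts the two age groups:

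| Variable | Analysis | Child-versus-adult contrast? |
|---|---|---|
| Primary (10.3.1) | 1-sided 95% lower bound against 0.60, one group | No |
| Duration of response (10.3.2) | Kaplan-Meier plot, interval for the median | No |
| Bleeding (10.3.2) | Number and percent by grade | No |

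**Inputs for the rule in a small subset.** The 1-sided 95% level and the 0.60 threshold are in section 10.3.1. The protocol gives neither the interval type nor the number of children, so both are varied below. It gives no figure for the subset that could be reproduced.

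**Best case: all n children respond.** No outcome gives a higher bound, so if this fails, every outcome fails.

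- Exact (Clopper-Pearson) lower bound: 0.05^(1/n).
- Wilson lower bound: n / (n + 1.645²).

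| n | Exact | Wilson |
|---|---|---|
| 3 | 0.368 | 0.526 |
| 4 | 0.473 | 0.597 |
| 5 | 0.549 | 0.649 |
| 6 | 0.607 | 0.689 |
| 10 | 0.741 | 0.787 |

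As a check on the exact column, the p-value for n out of n against 0.60 is 0.6ⁿ: 0.078 at n = 5 and 0.047 at n = 6. The rule is therefore out of reach for 5 or fewer children with an exact bound, and for 4 or fewer with a Wilson bound. Other formulas move the cut-off:

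- Agresti-Coull: 5 or fewer (5/5 gives 0.599).
- Mid-P: 4 or fewer (4/4 gives 0.562, 5/5 gives 0.631).
- Jeffreys: 3 or fewer (3/3 gives 0.556, 4/4 gives 0.638).
- Wald: any all-responder group passes, because the bound is 1.0 at every n.

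**Just above the cut-off (exact bound).** With 6 to 9 children all must respond, and with 10 children 9 must. The chance of meeting the rule at a true rate of 0.80 is 0.26 with 6 children and 0.38 with 10. At a true rate of 0.90 it is 0.53 and 0.74.

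**Illustration of how often the two groups would split.** Assume exact bounds, 31 adults, independent groups and the same true rate in both. Adults then need 24/31. At a common rate of 0.80 the adults pass with probability 0.730.

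- Up to 5 children: children fail with probability 1, so P(adults pass, children fail) = 0.730 × 1 = 0.73.
- 10 children: children fail with probability 1 − 0.376 = 0.624, so 0.730 × 0.624 = 0.46.
- 10 children, common rates 0.75, 0.80, 0.85 and 0.90: 0.36, 0.46, 0.42 and 0.26.

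**What a direct contrast would show.** Assume 25/31 adults respond. The 2-sided 95% Newcombe (score-based) interval for children minus adults is −0.25 to +0.36 with 5/5 children and −0.44 to +0.23 with 4/5.

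**The case against.** The strongest reply is that analyzing in the same manner ordinarily means the same endpoints and summaries, shown separately. Two response rates, two intervals and two Kaplan-Meier medians side by side are a descriptive look at differences, and section 10.2 states no null hypothesis. The effectiveness declaration in section 10.3.1 is made once, for the study. No sentence provides for a verdict in children, and the optional interim analysis in section 10.5.1 uses children for safety only.

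Much of this stands, and it keeps the point minor. It also rules out two stronger readings that a reader might infer:

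- **That 5 or fewer children must fail whatever happens.** This holds for an exact bound, and narrowly for Agresti-Coull. It does not hold for Wilson, mid-P, Jeffreys or Wald, and the protocol names no formula.
- **That the plan has a 73% false-positive rate for an age difference.** The protocol nowhere infers a difference from adults passing and children failing. With up to 5 children, the 0.73 is simply the adults' power under the assumed rate. It is not the error rate of any planned test.

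The reply does not remove the mismatch. Section 10.2 does not call the subset results descriptive, nothing in it excludes the 0.60 rule, and no interval for the difference is provided. Leaving the contrast to the SAP would be fair if the protocol were silent, but it states a method.

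**Conclusion.** The point holds at minor severity. The method prescribed for the child subset does not answer the question set for it, and this conclusion depends on no assumption about numbers. If the 0.60 rule is carried over literally, meeting or missing it says little about age. With an exact bound it cannot be met by 5 or fewer children, and with a Wilson bound by 4 or fewer.

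Whether the subset is that small cannot be told from the protocol, and neither can the interval type. The split probabilities (0.73 with up to 5 children; 0.26 to 0.46 with 10 across rates of 0.75 to 0.90) are illustrations under an exact bound, 31 adults and a common true rate. The documents do not support saying that the trial would declare the product ineffective in children. The primary analysis, the sample size and any stopping decision are unaffected.

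**What to change.** In section 10.2, replace the sentence that prescribes the method with:

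> For subjects aged 6 to 17 years, the number and percent of responders will be given with an exact 2-sided 95% confidence interval, and the difference in response rate from subjects aged 18 years and over with a 95% score confidence interval; these results are descriptive and the >0.60 rule of 10.3.1 will not be applied to this subset.

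The cost is one sentence and one table row, with no extra data or subjects. The sponsor gives up a formal effectiveness verdict in children, which a small subset could hardly support. The interval for the difference will be wide, as the 5/5 and 4/5 examples show. A test would add little: with 31 adults at 0.80 and children at 0.50, Fisher's test has power of 0.25 with 5 children and 0.43 with 10. Estimation with an interval is the realistic choice.
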